# Improving community case management of diarrhoea and pneumonia in district Badin, Pakistan through a cluster randomised study—the NIGRAAN trial protocol

**DOI:** 10.1186/s13012-014-0186-9

**Published:** 2014-12-10

**Keywords:** Community case management, Pneumonia and diarrhoea, LHW programme, Supervision, Implementation research, Pakistan

## Abstract

**Background:**

Diarrhoea and pneumonia contribute 30% of deaths in children under 5 in Pakistan. Pakistan’s Lady Health Workers Programme (LHW-P) covers about 60% of the population but has had little impact in reducing morbidity and mortality related to these major childhood killers. An external evaluation of the LHW-P suggests that lack of supportive supervision of LHWs by lady health supervisors (LHSs) is a key determinant of this problem. Project NIGRAAN aims to improve knowledge and skills of LHWs and community caregivers through supervisory strategies employed by LHSs. Ultimately, community case management (CCM) of childhood pneumonia and diarrhoea will improve.

**Methods/Design:**

NIGRAAN is a cluster-randomised trial in District Badin, Pakistan. There are approximately 1100 LHWs supervised by 36 LHSs in Badin. For this study, each LHS serves as a cluster. All LHSs working permanently in Badin who regularly conduct and report field visits are eligible. Thirty-four LHSs have been allocated to either intervention or control arms in a ratio of 1:1 through computer-generated simple randomisation technique. Five LHWs from each LHSs are also randomly picked. All 34 LHSs and 170 LHWs will be actively monitored. The intervention consists of training to build LHS knowledge and skills, clinical mentorship and written feedback to LHWs. Pre- and post-intervention assessments of LHSs, LHWs and community caregivers will be conducted via focus group discussions, in-depth interviews, knowledge assessment questionnaires, skill assessment scorecards and household surveys.

Primary outcome is improvement in CCM practices of childhood diarrhoea and pneumonia and will be assessed at the cluster level.

**Discussion:**

NIGRAAN takes a novel approach to implementation research and explores whether training of LHSs in supervisory skills results in improving the CCM practices of childhood diarrhoea and pneumonia. No significant harm to participants is anticipated. The enablers and barriers towards improved CCM would provide recommendations to policymakers for scale up of this intervention nationally and regionally.

**Trial registration:**

NIGRAAN is registered with the ‘Australian New Zealand Clinical Trials Registry’. Registration Number: ACTRN12613001261707

## Background

Pneumonia and diarrhoea are the leading causes of morbidity and mortality in children under 5, globally [1,2]. Together, these two early childhood illnesses account for one-fifth of the total number of deaths around the globe [3], the major proportion of which occur in the resource poor settings, most notably in Sub-Saharan Africa and South Asia [4-6].

By 2015, the United Nations Millennium Development Goal (UN MDG) 4 aims to reduce under 5 mortality by two-thirds. Pakistan is also a signatory to the UN MDGs and is among those nations who are far behind in achieving this target [7,8]. In Pakistan, around quarter of the children under 5 suffer from diarrhoea each year and one in six children experiences at least one episode of pneumonia annually [9]. These figures translate into around 0.7 million episodes of diarrhoea and more than 0.35 million episodes of pneumonia each year. Ironically, the coverage of proven lifesaving interventions like oral rehydration salt (ORS) for diarrhoea and antibiotics for pneumonia remains quite low [10]. In Pakistan, only 38% of the children receive ORS for diarrhoea and approximately 41% receive antibiotics for suspected pneumonia [9].

A ‘National Programme for Family Planning and Primary Healthcare’ commonly referred to as ‘Lady Health Workers Programme (LHW-P)’, was instituted in 1993–1994 in Pakistan. The programme aimed to provide maternal and child health services to the 60% underserved rural and remote population [11,12]. Under this programme, the women from the local community that met the specified eligibility criteria in terms of education and residence were recruited and trained as ‘lady health workers’ (LHWs) to serve as a ‘focal point of care’ for their respective communities [13]. On an average, an LHW usually serves around 100–150 households [14] translating into a population of approximately 1,000 individuals in her catchment area. The LHW-P also inducted ‘lady health supervisors’ (LHSs) to regularly monitor and supervise the LHWs. Each LHS usually supervises 20–25 LHWs. The LHS conducts random supervisory visits and collects monthly reports from the LHWs which provide information on type of cases encountered and relevant services provided. However, even after two decades, the overall impact on the health status at the population level has been very minimal especially in reducing early childhood disease burden and mortality attributable to diarrhoea and pneumonia.

The ‘Fourth External Evaluation of National Programme for Family Planning and Primary Health Care’ (FENP) conducted in 2008 provides insight into the causes and determinants of this stagnant mortality rate. Firstly, the LHWs lack skills and are not well prepared in managing cases of pneumonia and diarrhoea in the community. Only 8% LHWs are sensitised to the idea of looking for danger signs in the sick child and merely four out of five can correctly diagnose pneumonia. Secondly, the LHSs too have inadequate supervisory and clinical mentorship skills. Only 40% of LHWs receive the required feedback by their LHS and 59% of LHS pay a supervisory visit to their LHWs catchment area [15]. Figure 1 highlights the issues in the LHW programme which are amenable to the NIGRAAN intervention.

**Figure 1 Fig1:**
[figure not shown]
**Issues in LHW programme amenable to intervention [**
15
**].**

This implementation research project titled ‘NIGRAAN’ (Urdu word, meaning supervision) is designed to bridge these structural gaps in the existing LHW-P. The aim of NIGRAAN is to improve community case management (CCM) of childhood diarrhoea and pneumonia by health workers (LHWs and LHSs) and community caregivers (e.g. mothers) through strengthened supervision and mentorship by LHSs. The project utilises a cluster randomised design with each LHS as one cluster to estimate cluster level changes in CCM due to the intervention. Ultimately, this has the potential to reduce childhood morbidity and mortality due to diarrhoea and pneumonia.

### Primary outcome

The primary outcome is improvement in CCM practices of childhood diarrhoea and pneumonia.

This outcome pertains to the cluster level as the intervention targets LHSs and through them their respective LHWs. It will be achieved through the following effects of the NIGRAAN intervention:Improved knowledge, skills and supervisory processes among LHSs for CCM of pneumonia and diarrhoea in children under 5Improvement in LHW knowledge, skills and performance as a result of structured supportive supervision by LHSsImproved knowledge of community caregivers through interactions with LHWs and LHSs during community management of children with diarrhoea and pneumonia

## Methods

### Study design

This is a cluster randomised intervention trial consisting of three sequential phases:Pre-intervention: phase IFocus group discussions (FGDs) and in-depth interviews (IDIs) explore stakeholders’ (LHS/LHWs/policymaker) perspectives about the structural gaps in the LHW-P and health workers’ basic knowledge and skills related to CCM of childhood diarrhoea and pneumonia, etc. The findings would help to build an optimised intervention addressing deficient areas of knowledge and skills in the next phase. The baseline household survey (administered through a structured questionnaire) has been simultaneously administered to identify community caregivers’ practices related to childhood diarrhoea and pneumonia.An active case surveillance with a Global Positioning System (GPS) will also be initiated to identify, track and follow up all reported cases of childhood pneumonia and diarrhoea from the catchment households of randomly selected five LHWs/LHSs in both arms of the study (total 170 LHWs/34 LHS). Upon case identification, this surveillance will help to sample LHS and LHWs for assessment of their knowledge and skills related to CCM of diarrhoea and pneumonia. Knowledge assessment questionnaires (KAQs) and scorecards will be used for this purpose.Data obtained through baseline survey, scorecards, KAQs, FGDs and IDIs will be analysed to get consolidated results for the pre-intervention phase.Intervention: phase IIPhase II incorporates the refresher training of all LHS and execution of NIGRAAN specific intervention package (described below) for 9–12 months. The active case detection continues during this phase for periodic skill assessment of health workers through scorecards and KAQs and to distribute written feedback cards to LHWs as part of the NIGRAAN intervention package.Sample FGDs and IDIs will track the uptake of intervention by all stakeholders.Post-intervention: phase IIIPhase III includes an end-line household survey and qualitative data collection through FGDs and IDIs to identify barriers and enablers for NIGRAAN implementation and scale up.All the data obtained through the surveys, scorecards, KAQs, FGDs and IDIs during intervention and post-intervention phases will be analysed and results synthesised through method triangulation. Figure 2 provides an overview of NIGRAAN study phases.

**Figure 2 Fig2:**
[figure not shown]
**Overview of NIGRAAN study phases.**

### Study setting

District Badin in rural part of Sindh province, Pakistan, was chosen as the study site. It is approximately 4 hours one way by a feasible road drive from Karachi. The district has an operational LHW-P and the Department of Health, Government of Sind agreed to implement the project with the researchers. There are no previous similar projects currently being executed through the LHW-P in Badin. There are 1100 LHWs present in Badin supervised by 36 LHSs.

### Study participants

#### Policymakers and implementers

For the purpose of qualitative assessments at the provincial level, key decision-makers at the Provincial Department of Health and the Provincial Programme Implementation Unit of LHW-P will be approached. At the district level, ‘programme coordinators’ at the ‘District Programme Implementation Unit’ will be the point of focus.

#### Lady health supervisors (LHSs)

An LHS is the immediate female supervisor of LHWs, attached with the first-level care facility (FLCF). She has at least 8 years of schooling and is a local resident with a previous background of having worked as a lady health visitor (LHV) or an LHW. LHSs are recruited to provide supervisory support and ensure quality performance by the LHWs. The LHS collects progress reports, guides and addresses problems raised by LHWs. At the end of each month, the supervisor compiles evaluation reports and submits these to the districts. LHSs fulfilling the following criteria will be involved in project NIGRAAN:LHS who is performing duties as part of LHW programme within geographical boundaries of District BadinLHS whose employment terms are permanentLHS who conducts ‘field monitoring visits’ and reports them to the district level authorities.

LHSs in this study will be involved primarily for periodic assessment of their skills pre and post intervention and in implementing the NIGRAAN intervention by providing written feedback cards to their assigned LHWs.

#### Lady health workers

LHWs are salaried staff, preferably married and educated (minimum 8 years of schooling). They are mostly permanent residents of the area, well known and are familiar with the houses assigned to them in their respective catchment areas. They are trained and supervised by LHSs according to a predefined checklist. A trained LHW provides basic health care to her own community. Each LHW maintains her register, reports to her assigned LHS and submits a monthly report based on specified LHW-P management information tools. The inclusion criteria for LHWs in project NIGRAAN are as follows:LHW who is performing duties as part of LHW programme within geographical boundaries of District BadinLHW who provides services to the households as per LHW programme guidelines and reports the relevant data to the respective supervisor/LHS

LHWs in this study will be involved primarily for periodic assessment of their skills pre and post intervention and in implementing the NIGRAAN intervention by actively reporting cases of pneumonia and diarrhoea to their respective LHSs.

#### Community caregivers

Community caregivers include mothers of children under 5 years of age and/or other caregivers for children under 5, in the population of the study site. The inclusion criterion for community caregivers is:Community caregiver/parent/guardian permanently residing in the household falling under the geographical scope/coverage area of the LHW enrolled into the studyCommunity caregiver residing in a household that has at least one child under 5 years of age

Pre- and post-intervention household surveys will assess their knowledge and practices for management of childhood diarrhoea and pneumonia.

### Sampling

Our sample size is estimated based on the expected number of children under 5 who experience an episode of pneumonia per year. The estimated incidence of pneumonia among children under 5 in Pakistan is 0.41 episodes per child-year (e/cy) [9].

#### Sample estimates

It was estimated that to achieve 80% power for estimating the effect of the intervention at 95% confidence interval and intra-cluster correlation coefficient of 0.122, 17 LHSs (1 LHS = 1 cluster) will be required for intervention and non-intervention arms each.

Five (5) LHWs will be selected in each cluster (85 each in intervention and control arm). These 170 LHWs are required to be able to detect the required number of diarrhoea and pneumonia cases in their catchment households for continuous skill assessment of LHWs and LHSs and to execute the intervention.

The sample for qualitative FGDs was drawn from the above pool of 170 LHWs at random with a target of 8–10 participants in each FGD.

To attain 80% power with 95% confidence interval for the baseline household survey, we estimated that at least 8,500 households will have to be selected in each arm (one LHW covers approximately 100 households). With a systematic randomisation of taking every fourth (4th) household with an expected number of one child under 5 years per household, at least 2,125 households will have to be approached in the baseline/endline survey in each arm to assess community caregiver practices for management of childhood diarrhoea and pneumonia. NIGRAAN baseline survey sampling strategy is depicted in Figure 3.

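### The household survey's 80% power is attached to 8,500 households per arm, which is the catchment of the sampled LHWs and not a power result; only 2,125 per arm are surveyed

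*Protocol article*

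**What the plan says.** The protocol article makes two power statements under Sample estimates.

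- **Trial level.** The article claims "80% power for estimating the effect of the intervention at 95% confidence interval" and, with an "intra-cluster correlation coefficient of 0.122, 17 LHSs (1 LHS = 1 cluster) will be required for intervention and non-intervention arms each".
- **Household survey.** "To attain 80% power with 95% confidence interval for the baseline household survey", the article continues, "we estimated that at least 8,500 households will have to be selected in each arm (one LHW covers approximately 100 households"). It then thins the households: "With a systematic randomisation of taking every fourth (4th) household with an expected number of one child under 5 years per household", so that "at least 2,125 households will have to be approached in the baseline/endline survey in each arm".

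The same section fixes the number of health workers: "Five (5) LHWs will be selected in each cluster (85 each in intervention and control arm"). Table 2 ties the primary outcome to change in caregiver practices between the baseline and end-line household surveys. The Sampling section gives the general basis as follows: "Our sample size is estimated based on the expected number of children under 5 who experience an episode of pneumonia per year", with an incidence of 0.41 episodes per child-year. Neither power statement gives a target difference or a control proportion for caregiver practices.

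**The concern.** A figure introduced as what 80% power requires should come from a power calculation and should be the number actually studied. Here the survey uses a quarter of the stated number, and the explanation in brackets (households per LHW) points to a head count of the catchment. The one epidemiological input named, pneumonia incidence, is an event rate and not a caregiver-practice proportion.

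What is at stake is how the primary result will be read. Thousands of households alongside 80% power suggest that differences of a few percentage points are detectable. With 17 clusters per arm and this ICC, they are not. A null result could then be taken as evidence of no effect when moderate effects were not excluded.

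**Working it through.** **Inputs from the protocol article.** 17 clusters per arm; 5 LHWs per cluster; about 100 households per LHW; one household in four; ICC 0.122; 80% power; 95% confidence, taken here as two-sided 5%.

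**Assumed inputs.** Control proportion 38% or 41%. These are the national ORS and antibiotic coverage figures in the Background, which the article does not name as design inputs. Cluster sizes are taken as equal.

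**1. Where the two counts come from**

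- 17 x 5 = 85 LHWs per arm.
- 85 x 100 = 8,500 households.
- 8,500 / 4 = 2,125 households.
- 2,125 / 17 = 125 households per cluster.

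Both stated counts are reproduced exactly from the sampling structure. No effect size, control proportion, ICC or power level enters either. The 80% itself cannot be reproduced, because no target difference is given.

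**2. What the household count does to information**

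Design effect DE = 1 + (m - 1) x ICC, and effective n per arm = 17m / DE.

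| Households per arm | m | DE | Effective n per arm |
|---|---|---|---|
| 2,125 | 125 | 1 + 124 x 0.122 = 16.13 | 2,125 / 16.13 = 131.8 |
| 8,500 | 500 | 1 + 499 x 0.122 = 61.88 | 8,500 / 61.88 = 137.4 |
| no limit | – | – | 17 / 0.122 = 139.3 |

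Four times the households adds fewer than 6 effective observations per arm.

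**3. Detectable difference at 80% power, end-line comparison only**

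Non-centrality = (p1 - p0) / sqrt{[p0(1 - p0) + p1(1 - p1)] / effective n}, with a two-sided t-test on 2 x 17 - 2 = 32 degrees of freedom.

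Example with 2,125 households, from 41% to 58.5%: variance sum 0.2419 + 0.2428 = 0.4847; standard error sqrt(0.4847 / 131.8) = 0.0606; non-centrality 0.175 / 0.0606 = 2.89; power 80%.

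| Households per arm | From 38% | From 41% |
|---|---|---|
| 2,125 | 17.5 points | 17.5 points |
| 8,500 | 17.1 points | 17.2 points |

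The normal approximation gives about 17 points in each cell.

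**4. Power at 2,125 per arm for differences chosen here for illustration**

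From 38-41%, power is about 36% for +10 points and 67% for +15 points. With 8,500 it would be about 37% and 68-69%. The cut to one household in four therefore costs under 2 points of power.

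**5. Sensitivity of the 17 to 18 points**

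- *Fewer contributing households.* If only one household in six had an ill child (assumed), m = 125 / 6, or about 21. DE is then about 3.42, effective n about 104, and the detectable difference about 19.7 points.
- *Baseline adjustment.* If cluster-level baseline and end-line values correlate at 0.3, 0.5 or 0.7 (assumed), the variance is multiplied by 1 - r². The detectable difference from 41% falls to about 16.7, 15.2 or 12.6 points.
- *Clustering ignored.* The detectable difference would be about 4.2 points with 2,125 and 2.1 with 8,500. The design does not justify this reading, but the raw household counts invite it.

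**The case against.** The strongest reply is that 8,500 was meant as the sampling frame and 2,125 as the sample. The remark on households per LHW and the every-fourth-household step both point that way, and the sampling figure (Figure 3) is not available to check. The 8,500 sentence also speaks of the baseline survey, whereas power for the intervention effect is stated separately through 17 clusters per arm and an ICC of 0.122. On this view the design is untouched. Most of this stands: nothing here contradicts the 17-cluster statement, and the frame reading is probably what was meant. It does not rescue the sentence, because a frame does not attain power, and the same survey, repeated at end-line, measures the primary outcome.

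A reader might infer two stronger things. One is that surveying 2,125 instead of 8,500 undermines the power; step 2 shows that at this ICC it barely matters. The other is that the trial is underpowered. The article sets no target difference, so there is nothing to fall short of: the 36% and 67% refer to differences that the article never proposed, from control values that it never adopted. Leaving an effect size out of a condensed article is also not an error in itself. The fault is that the article states a power requirement and attaches it to a number that is not one.

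**Conclusion.** The point holds as an error in the stated basis of the sample size. The 8,500 households per arm are the catchment of 85 LHWs, they are not needed for 80% power, and they are not the number surveyed. At the article's own ICC and cluster count, the effective sample is about 132 per arm with 2,125 households and about 137 with 8,500, so the number of clusters governs power and the household count hardly matters. No underpowering is shown.

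The figure of about 17 to 18 points depends on a 38-41% control value, an end-line-only comparison, equal cluster sizes and an outcome from every household. It rises to about 20 points if only about 21 households per cluster contribute, and falls with baseline adjustment. The catchment arithmetic and the effective sample sizes do not depend on the control value.

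**What to change.** Under Sample estimates:

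1. Describe 8,500 households per arm as the sampling frame (85 LHWs x about 100 households) and remove the statement that 80% power requires them.
2. Restate the survey's power for 17 clusters x 125 households (2,125 per arm) with ICC 0.122 and two-sided 5%. Give the sponsor's target difference and the control proportion for the caregiver practice concerned, and give the same target in the sentence on the number of clusters.
3. If no target was set, say so and give the detectable difference with its assumptions: about 17 to 18 points at 80% power from an assumed 38-41% control value, end-line only and every household contributing; about 20 points if about one household in six has an ill child; smaller with baseline adjustment, by an amount that depends on the assumed correlation.

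The cost is a few sentences. Clusters, households and procedures stay as they are, and no extra participants are needed. The downside is that the stated sensitivity will look less favourable than the household count suggests.

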**Figure 3 Fig3:**
[figure not shown]
**Overview of NIGRAAN sampling strategy for baseline survey.**

#### Allocation to intervention

LHSs were allocated to clusters based on a parallel design with 1:1 ratio. The allocation of 34 LHSs to intervention/control arm clusters was blinded at the cluster level and carried out through computer-generated randomised tables in computer software MS Excel. The process was carried out by a person not otherwise involved in the study.

